#### Analysis of salivary cortisol

To obtain cortisol levels the saliva samples will first be thawed and centrifuged at 3000 rpm for 15 minutes at room temperature. The levels will be determined in the HKU Clinical Oncology Lab using an enzyme-linked immunosorbent assay (EIA) kit (Salimetrics Inc., USA). The assay sensitivity for this kit is 0.007 g/dl (i.e. 0.193 nmol/l) and the intra- and inter-assay coefficients of variation are 3% and 10%, respectively.

Due to the skewed distribution of salivary cortisol data, a natural logarithm will be used to normalize raw cortisol data. Mean cortisol levels will be calculated across four collection time points. Total cortisol levels will be expressed as area under the curve (AUC), and diurnal cortisol rhythm will be calculated by linear regression analysis of log-transformed cortisol levels at time of collection.

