### Schizophrenic Symptoms and the HPA Axis

Salivary cortisol, a neuroendocrine indicator of stress and immunity, can provide insight into the possible physiological mechanisms underlying schizophrenia [16]. Patients with schizophrenia tend to have altered cortisol levels and stress responses, though studies conducted thus far have demonstrated both hyper- and hypo-function of the hypothalamic–pituitary–adrenal (HPA) axis which regulates cortisol levels [26]. Abnormally blunted cortisol responses have also been recorded in patients with schizophrenia [27]. Both hyper- and hypo-activity of the HPA axis have adverse effects on physical and psychological health. For patients with schizophrenia, increased cortisol levels are associated with more severe negative symptoms [28] and worse cognitive functioning in terms of verbal memory [29]; blunted cortisol responses are also associated with poorer quality of life [30]. While a previous study has demonstrated the effectiveness of Tai-chi in lowering salivary cortisol concentrations [31], the effects of lowered cortisol concentrations on symptoms, and other physical and psychological deficits that impair patient well-being, are virtually unknown. Alleviation of symptoms, other deficiencies and psychological health challenges can benefit patients’ overall functioning and quality of life. Tai-chi has been shown to confer these benefits in a number of chronic conditions [32].

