3.*Digit Span – Wechsler Adult Intelligence Scale, Third Edition – Chinese version (WAIS-III)* [37] *–* The digit span sub-scale is composed of two parts: forward movement of digits, and backward movement of digits. Participants will be invited to repeat movements of 3*–*9 digits forward and 2*–*9 digits backward. Clinically, the sub-scale evaluates participants’ short-term memory, attention, and concentration.4.*Barthel’s Activities of Daily Living (ADL) index – Chinese version (Barthel’s ADL)* [38] Barthel’s ADL index evaluates basic self-care. The index comprises 10 tasks, including feeding, transferring, grooming, toilet use, bathing, walking, climbing stairs, dressing, and bowel and bladder continence. The items are weighted according to a scheme developed by the authors.5.*Lawton’s Instrumental Activities of Daily Living (IADL) scale – Chinese version* [39] – This self-report scale covers 8 domains of complex daily life, such as ability to use the telephone, shopping, food preparation, housekeeping, laundry, traveling on public transport, self-medication, and the ability to handle finances.6.*Stress*6.1Perceived stress scale (PSS) [40] – The PSS measures how often participants experience general stressfulness within a given month on a 10-item, 5-point Likert scale. Higher scores indicate greater stress. The Chinese version of the PSS was translated and utilized by the research team with good internal consistency.6.2Salivary cortisol – Collection will be conducted by participants themselves under the guidance of mental health professionals. Saliva samples will be collected at four prescribed times (upon awakening, 30 minutes post-awakening, at 11:30 am and at 7:30 pm) using the collection device “Salivette” (Starstedt, Ag & Co., Nümbrecht, Germany), which includes a cotton swab to place under the tongue. Smoking, eating and drinking will be prohibited for half hour prior to saliva collection. The samples collected will be stored at −20°C until analysis.6.3Daily condition measures with salivary cortisol – Measures of participants’ health-related behaviors and activities on the day of saliva collection will be collected in conjunction with salivary cortisol. These measures include (i) self-reported sleep quantity that day (hours of sleep at night and nap hours), (ii) subjective sleep quality rated on a scale of 1 to 10, (iii) smoking habit and the number of cigarettes consumed that day, (iv) alcohol/coffee drinking habits and the approximate amount consumed that day, and (v) subjective evaluation of dietary habits and the quality of diet on the day of collection rated on a scale of 1 to 10. All the above measures will affect the diurnal cortisol rhythm and hence must be taken into account during data interpretation.

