#### Relationship between cortisol levels and physical and psychological deficits

Using baseline data from all participants, correlation analyses will be used to explore the interrelationship between diurnal cortisol patterns and subjective stress, psychiatric symptoms, motor deficits, memory test and general functioning.

To trace individual changes in salivary cortisol levels over time, and to evaluate the complex relationships between different variables, the two-level individual growth curve model [42] and MPlus software will be used for analysis. This method is a variant of multiple regression modeling appropriate for the nested structure of our data sets. In the study, salivary cortisol measures at four time points over the day are nested within participants.

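### Read plainly, the diurnal cortisol slope is one line through all four samples, so any rise 30 minutes after awakening is mixed into it

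*Protocol article*

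**What the plan says.** In the protocol article, Instruments, item 6.2, four saliva samples are scheduled per day: "upon awakening, 30 minutes post-awakening, at 11:30 am and at 7:30 pm".

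Analysis of salivary cortisol starts from a log scale ("a natural logarithm will be used to normalize raw cortisol data") and then names three summaries:

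- a mean: "Mean cortisol levels will be calculated across four collection time points";
- a total, expressed as area under the curve;
- a rhythm: "diurnal cortisol rhythm will be calculated by linear regression analysis of log-transformed cortisol levels at time of collection".

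The sentence on the mean says how many samples it uses. The sentence on the rhythm does not, but it excludes none and gives no separate term for the period just after waking.

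The next section, Relationship between cortisol levels and physical and psychological deficits, correlates diurnal cortisol patterns at baseline with stress, symptoms, motor deficits, memory and functioning. It also plans a two-level growth curve model in which "salivary cortisol measures at four time points over the day are nested within participants". The form of time in that model is not given.

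**The concern.** The first two samples are half an hour apart, and the other two follow hours later. A straight line on log cortisol describes a steady decline over the day. If the level at 30 minutes stands above that decline, the line absorbs the excess as extra steepness. Two participants with the same daytime decline but different rises after waking then get different slopes, and the slope alone cannot show which feature produced the difference.

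What is at stake is the interpretation of one cortisol summary. A baseline correlation with the slope, or an arm difference in it, could reflect the post-awakening change, the daytime decline or both. The two samples that could separate them are already collected, but none of the three listed summaries uses them for that.

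**Working it through.** The article gives no figure for the slope, so there is none to reproduce. The check is the algebra of a least-squares slope at the stated times.

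**Inputs from the article:** the four sampling times (Instruments, 6.2); natural log and linear regression on time (Analysis of salivary cortisol).

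**Assumptions, because the article does not give them:** waking at 7:00 (range 6:00 to 8:00); a log-linear decline of -0.05, -0.10 or -0.15 per hour; a level at 30 minutes that stands 25%, 50% or 100% above that decline.

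**Step 1, weights.** The slope is the sum of w_i × ln(cortisol_i), with w_i = (t_i - mean t)/Sxx.

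- Times in hours from waking: 0, 0.5, 4.5, 12.5. Mean = 17.5/4 = 4.375.
- Sxx = 19.141 + 15.016 + 0.016 + 66.016 = 100.19.
- Awakening: -4.375/100.19 = -0.0437.
- 30 minutes: -3.875/100.19 = -0.0387.
- 11:30 am: 0.125/100.19 = +0.0012.
- 7:30 pm: 8.125/100.19 = +0.0811.

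The 30-minute sample carries 0.0387/(0.0437 + 0.0387) = 47% of the weight of the two morning samples.

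**Step 2, shift from a rise r.** Shift = -0.0387 × ln(1 + r).

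| Rise | ln(1 + r) | Shift per hour |
|---|---|---|
| 25% | 0.2231 | -0.0086 |
| 50% | 0.4055 | -0.0157 |
| 100% | 0.6931 | -0.0268 |

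For a 50% rise, waking at 6:00 gives -0.0372 × 0.4055 = -0.0151, and waking at 8:00 gives -0.0399 × 0.4055 = -0.0162.

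Here r is measured against the decline line. If it is measured against the awakening sample, the departure is larger by half an hour of decline. At -0.10 per hour that is 0.05, which adds 0.0387 × 0.05 = 0.0019 to the size of the shift.

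**Step 3, relative size for a 50% rise, waking at 7:00.** 0.0157/0.15 = 10%; 0.0157/0.10 = 16%; 0.0157/0.05 = 31%.

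**Step 4, a difference in the rise.** 50% against 25%: 0.0157 - 0.0086 = about 0.007 per hour, with the same daytime decline in both. That is 5%, 7% or 14% of slopes of -0.15, -0.10 or -0.05.

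**Step 5, the slope without the 30-minute sample.**

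- Times 0, 4.5, 12.5. Mean = 17/3 = 5.667. Sxx = 32.111 + 1.361 + 46.694 = 80.17.
- Weights: -0.0707, -0.0146, +0.0852.
- Under a log-linear decline these weights return the true slope whatever the level at 30 minutes.
- Ratio of standard errors under independent noise: sqrt(100.19/80.17) = 1.118, about 12% more.
- Weight on the awakening sample: from -0.0437 to -0.0707, 62% more.

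**The case against.** **The regression sentence does not say which samples enter.** This is true, and a journal article may leave that detail to the full protocol. What stands is that using all four is the plain reading, since nothing shown removes one. If the full protocol restricts the regression, the point lapses.

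**The documents describe no rise at 30 minutes.** This also stands. They give a sampling time and no expected profile, so every rise used here is an assumption. The mixing does not depend on a particular value: any departure from the line at that sample moves the slope.

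**A rise common to all arms cancels.** Correct. The 10% to 31% is an error in the absolute slope and not in a treatment contrast. Only differences in the rise matter between arms, and the example gives about 0.007 per hour. Cancellation does not help the baseline correlations, which rest on differences between participants.

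**The alternative has its own weakness.** Leaving the sample out puts more weight on the awakening sample, which participants collect themselves under guidance. The separate rise measure shares that sample with the slope, so an error in it affects both. This is a real trade-off.

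**A stronger reading that the documents do not support.** The background states "Abnormally blunted cortisol responses have also been recorded in patients with schizophrenia", and a reader might infer that it singles out the awakening response and that omitting a summary of it is an error. That section speaks of stress responses in general and does not tie the remark to awakening. Research objectives names salivary cortisol levels, and the awakening response is not a named outcome. A reader might also infer that the growth model shares the fault; its time form is not stated, so that cannot be said.

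**Conclusion.** The point holds as a cheap improvement of minor to moderate importance, confined to the cortisol slope and the analyses that use it. On the plain reading, the slope combines the daytime decline with whatever happens in the first half hour after waking. For an assumed 50% rise and waking between 6:00 and 8:00, the absolute slope shifts by about -0.015 to -0.016 per hour. The more relevant figure for correlations or arm comparisons is the effect of a difference in the rise, about 0.007 per hour for 50% against 25%.

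These sizes rest on assumed wake times, rises and true slopes. The weights follow from the stated schedule once a wake time is assumed. Sample size, the non-cortisol outcomes, and the cortisol mean and area under the curve are not touched by this point.

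**What to change.** State which samples enter the diurnal slope, and fit it on the awakening, 11:30 am and 7:30 pm samples. Report ln(30-minute level) minus ln(awakening level) as a separate summary, labelled exploratory.

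If the growth curve model uses linear time, add an indicator for the 30-minute sample. Let its coefficient differ by arm and, where the data allow, by participant, because a single common coefficient removes only the average rise.

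The cost is a change of analysis wording, with no new samples. Sampling error of the slope from independent noise rises by about 12%. The awakening sample's weight goes from about -0.044 to -0.071, so a mistimed first sample does more harm. Recording the actual collection times and showing the four-sample slope as a sensitivity analysis would let a reader judge that trade-off.

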#### Relationship between cortisol levels and physical and psychological deficits

Using baseline data from all participants, correlation analyses will be used to explore the interrelationship between diurnal cortisol patterns and subjective stress, psychiatric symptoms, motor deficits, memory test and general functioning.

To trace individual changes in salivary cortisol levels over time, and to evaluate the complex relationships between different variables, the two-level individual growth curve model [42] and MPlus software will be used for analysis. This method is a variant of multiple regression modeling appropriate for the nested structure of our data sets. In the study, salivary cortisol measures at four time points over the day are nested within participants.

## Discussion

While physical exercise has been researched extensively, this RCT will represent one of the first investigations into mind-body exercises in patients with schizophrenia. The results of a pilot study demonstrated attenuated deterioration in motor coordination and daily functioning in patients practicing Tai-chi. With a larger sample size, and using an exercise group for comparison, the aims of this RCT are to confirm previous findings and to provide new insight into how Tai-chi may provide unique benefits to patients with schizophrenia, above the effects of moderate aerobic exercise. Analysis of salivary cortisol levels will elucidate the effect of Tai-chi on physiological stress. The results will establish the feasibility and efficacy of integrating mind-body exercises into routine care as complementary treatment for psychiatric conditions.
